## Methods

The following protocol (version 5, September 9th 2022) follows SPIRIT guidelines for reporting protocols (see Additional file 1). In this four-arm parallel-group RCT of SRG, MT and MiCBT versus an active control (equal allocation ratio), we will deliver the interventions to small groups of smokers to maximise the potential cost-effectiveness. 6-months of these interventions will be followed by 6-months of online peer support and a further 6-month follow-up period. The control group will be directed to optional resources including counselling (Quitline) and information about pharmacological aid. We aim to: (a) test the efficacy of the three interventions (SRG, MT and MiCBT) for smoking cessation and (b) levels of resilience in low SES groups and how this changes during exposure to the interventions, (c) measure the cost-effectiveness and cost-utility of the interventions in low SES groups, and (d) undertake a process evaluation of the different interventions in low SES groups. We hypothesise the following:H1: The proportion of participants who report 14-day period abstinence from smoking at 6 months will be significantly higher for each intervention group compared to the control group.H2: Amongst participants that report 14-day period abstinence at 6 months, the proportion of participants who report 14-day period abstinence at 12 months will be significantly higher for each intervention group compared to the control group.H3: The proportion of participants who report 14-day period prevalence abstinence from smoking at 6 months post-trial (18 months from baseline) will be significantly higher for each intervention group compared to the control group.H4: Levels of resilience measured by the Connor-Davidson CD-25 [43] and ENRICHD Social Support Inventory [44] will be significantly higher for each intervention group compared to the control group at 6, 12 and 18 months post randomisation.H5: The interventions will improve smoking cessation and QALYs at a reasonable and acceptable incremental cost.

In addition, we pose the following research questions for the qualitative component of the study (that pertains to the process evaluation):RQ1: Have the different interventions been implemented and received as intended?RQ2: What are the barriers and facilitators associated with the first research question?RQ3: For whom, and in what circumstance were the interventions effective (and cost-effective) or not, and why?

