### Sample size and power analysis

For the primary outcome of smoking cessation, 182 participants per group is powered to detect an 11.6% difference [47] in the smoking abstinence rates between groups (with 80% power, alpha = 0.05 (two-tailed test) We will account for a 10% drop-out rate, and thus aim to recruit 203 per group (N = 812). Contextually, the smoking cessation rates we used for the sample size calculation (MT = 25.2%, usual care = 13.6%) represent a meaningful population health treatment effect doubling of the rate of successful quit attempts for the lowest SES group (11.4%; [9]).

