#### Secondary outcomes—investigating the mechanisms influencing behaviour change

##### Internal and external resilience

The 25-item Connor-Davidson CD-25 scale measures the internal resilience construct of the psychosocial model of resilience. [43] Connor and Davidson [43] found evidence for the convergent validity of the scale and observed satisfactory internal consistency (α = 0.89) in the general population and satisfactory test–retest reliability (intraclass coefficient = 0.87) in a clinical sample.

The 7-item ENRICHD Social Support Inventory [44] will be used to measure self-reported external resilience. Mitchell [44] found evidence of convergent validity and observed satisfactory internal consistency (⍺ = 0.86). Vaglio et al. [49] observed satisfactory test–retest reliability over a one-month interval (intraclass correlation = 0.94).

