#### Analyses

All analyses will use Stata (version 17.0 [69]). This will be undertaken blinded to the participants’ group allocation. Mixed-effects modelling will be used to assess the effect of the interventions on primary and secondary outcomes. This approach accounts for the correlation of the data from repeat measures over time and reduces bias caused by missing data at one or more time points for each participant. In addition, we will develop prediction models to determine whether levels of internal and external resilience measured at baseline predict smoking cessation. As an exploratory analysis, we will also perform mediation analyses to determine the direct and indirect effects of the separate components of each intervention on the primary and secondary outcomes.

For outcomes assessed at a single time-point, we will assess the difference between the four groups at that time. For outcomes assessed at repeat time points, we will assess differences between the four groups at each time point, with adjustment for multiple comparisons. We will assess binary outcomes using mixed-effects logistic regression and continuous outcomes using linear mixed-effects regression. In repeated measures, we will treat time as a categorical variable, and the model will include fixed-effects for time and group. Subgroup analysis will be undertaken to test whether people with a critical level of resilience are more likely to stay quit than those that do not meet this level. The main analyses will be performed on a per-protocol basis. Our intention-to-treat population will be defined as all participants that were randomised and also completed the baseline survey. We will perform a sensitivity analysis on a modified intention-to-treat basis and impute missing data where possible. Where more than 10% of data are missing, we will also perform multiple imputation as a sensitivity analysis to account for possible bias in estimates caused by missing data. Missing smoking data will be presumed MNAR and analysed as continued smoking. Hypothesis testing will be performed using 2-tailed tests with a Type 1 error rate of alpha = 0.05, and 0.05/3 = 0.0167 when assessing each outcome across time to account for the repeated testing at 6, 12, and 18 months. We will make further adjustments for multiple comparisons (e.g., 3 comparisons with control) depending on each outcome.

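### The fixed 0.0167 threshold for the 6-, 12- and 18-month tests is valid, but Holm's procedure is more powerful at the same 5% error rate for the secondary outcomes

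*Protocol article*

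**What the plan says.** The Analyses section gives the general level: "Hypothesis testing will be performed using 2-tailed tests with a Type 1 error rate of alpha = 0.05". For an outcome tested over time it then sets "0.05/3 = 0.0167 when assessing each outcome across time to account for the repeated testing at 6, 12, and 18 months". The method is not named, but dividing 0.05 by the number of tests and holding each test to the result is Bonferroni. The section adds: "We will make further adjustments for multiple comparisons (e.g., 3 comparisons with control) depending on each outcome". No method is given for that further step.

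The hypothesis to which the rule most plainly applies is H4 in the Methods section, on the Connor-Davidson and ENRICHD scales. It predicts that resilience "will be significantly higher for each intervention group compared to the control group at 6, 12 and 18 months post randomisation". The primary outcome, smoking cessation, is defined at 6 months only, and its sample size is stated "with 80% power, alpha = 0.05 (two-tailed test").

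**The concern.** Under a fixed threshold, an outcome that clears 0.0167 at one visit gets no credit for that at the other two. A p-value of 0.02 at 18 months counts as a failure even when the 6- and 12-month results are overwhelming. Holm relaxes the later steps once an earlier one succeeds, and it needs no assumption about the dependence between tests.

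This matters for H4 because it names all three visits. If the intervention really raises resilience throughout, the fixed rule will more often declare the effect at only one or two of them. H4 would then be reported as partly unsupported because of the testing rule rather than the data.

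**Working it through.** **1. The plan's figures.** 0.05/3 = 0.0167, as stated. The 80% benchmark used below is the plan's own design power. With 25.2% versus 13.6%, the mean rate is 0.194, and the pooled normal formula gives n = [1.960 × √(2 × 0.194 × 0.806) + 0.842 × √(0.252 × 0.748 + 0.136 × 0.864)]² / 0.116² = 181.2, so 182 per group. Power at n = 182 is 0.802.

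**2. Inputs for the comparison.**
- Three two-sided tests, one per visit, with a total error of 0.05 (Analyses).
- Effect size: the article gives none for the resilience scales. As an illustration, each true effect is set to 80% power at 0.05, so the test statistic has mean 1.960 + 0.842 = 2.802.
- Correlation between the three test statistics: not given. Assumed 0.5, 0.7 and 0.87. The last borrows the scale's reported reliability ("intraclass coefficient = 0.87) in a clinical sample"), which is not a six-month correlation in this trial.

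**3. Fixed rule, power per time.** The two-sided critical value at 0.0167 is 2.394. Power = Φ(2.802 − 2.394) = Φ(0.408) = 0.658, whatever the correlation.

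**4. Holm.** Order the three p-values and compare the smallest with 0.05/3 = 0.0167, the next with 0.05/2 = 0.025 and the largest with 0.05, stopping at the first failure. The first step equals the fixed rule and later steps are looser, so Holm never rejects less. Simulation of 1,000,000 trivariate normal statistics, with the effect real at all three times, gives:

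| Correlation | Per time, fixed | Per time, Holm | All three, fixed | All three, Holm | At least one, either rule |
|---|---|---|---|---|---|
| 0.5 | 0.658 | 0.735 | 0.42 | 0.59 | 0.874 |
| 0.7 | 0.658 | 0.728 | 0.48 | 0.64 | 0.825 |
| 0.87 | 0.658 | 0.718 | 0.54 | 0.68 | 0.768 |

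**5. Less favourable patterns, same correlations.**
- Effect at two times only: 0.66 to about 0.69 per affected time.
- Effect at 6 months only: 0.66 to 0.66.
- Effect halving at each visit: 0.66 to 0.66 at 6 months, 0.16 to 0.20 at 12 months, and 0.05 to 0.08-0.10 at 18 months.

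**6. Role of correlation.** With no true effects, the family-wise error of the fixed rule is 0.044, 0.039 and 0.032 at the three correlations. Holm's is identical, because its first rejection also requires 0.0167. Holm's gain per time also shrinks as correlation rises: about 9 points at zero correlation (0.658 to 0.750), 8 at 0.5 and 6 at 0.87.

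**The case against.** The strongest objection is that nothing in the plan is wrong. The threshold is stated in advance, its arithmetic is right, it controls the error rate, and it bears mainly on secondary outcomes. That stands, and it limits this point to a suggestion about efficiency.

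A reader might infer that the loss is caused by strong correlation between visits and that Holm recovers it. The documents and the arithmetic do not support this. Holm ignores correlation and leaves the same error unused when there are no effects. Recovering that part would need a method based on the joint distribution of the tests; a single-step threshold of that kind would be about 0.019 at correlation 0.5 and 0.029 at 0.9. Nor is strong correlation documented: the article reports test-retest figures of 0.87 and 0.94 from other samples, the second over one month, and neither describes six-month intervals in this trial.

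The illustration is also the favourable case. Group sessions end at 6 months and peer support at 12, so fading effects are plausible, and the gain is then small. Even in the favourable case Holm misses at least one visit in 32-41% of trials. This objection stands in full.

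If H4 is read as a single claim that requires all three visits together, testing each at 0.05 already controls the error of that joint claim and is slightly more powerful than Holm (0.61, 0.66 and 0.71 against 0.59, 0.64 and 0.68). That is correct. But the Analyses section plans a separate verdict at each time point, and for separate verdicts Holm is the relevant comparison.

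Finally, the promised adjustment for the three comparisons with control means that neither 0.66 nor 0.72-0.74 is the trial's actual power. That too is right; the figures only compare the two rules on equal terms.

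**Conclusion.** The point holds as a modest efficiency improvement. For outcomes tested at 6, 12 and 18 months, Holm is never less powerful than the fixed 0.0167 and has the same 5% guarantee. In the illustration, the gain is 6 to 8 points per time and 13 to 17 points for showing the effect at all three times. It falls to about 3 points per affected time with two real effects and about zero with one, and the chance of at least one rejection is the same under both rules. The recovery is partial: power per time does not return to 0.80.

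These sizes rest on an assumed effect at each visit and assumed correlations. That Holm never rejects less rests on neither.

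The finding does not extend to the primary analysis. A reader might take Holm as a remedy for the 6-month cessation test, but that outcome has a single time point and was sized at 0.05, so it should not be made to depend on later visits.

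**What to change.** For secondary outcomes tested at 6, 12 and 18 months, chiefly the two H4 resilience scales, replace the fixed 0.0167 with Holm across the three times: ordered p-values against 0.0167, 0.025 and 0.05, stopping at the first failure. Apply it within whatever level remains after the planned adjustment for the three comparisons with control; if that level is a, the steps are a/3, a/2 and a. State that the 6-month primary cessation test is outside this family. Report unadjusted 95% confidence intervals beside the Holm-adjusted p-values.

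The cost is about one sentence, with no extra data, visits or participants. It should be settled before outcomes are seen by arm. There are two small downsides. Simple simultaneous confidence intervals no longer match the tests exactly. A 6-month p-value between 0.0167 and 0.05 on these outcomes cannot be settled until the later visits are analysed.

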#### Cost-effectiveness

A cost-effectiveness model will be used to estimate all important differences in costs and benefits between the three trial arms if there is significant uncertainty regarding the most cost-effective option based on the within trial analysis. Published smoking cost-effectiveness models will be reviewed to identify the most valid available model from an Australian perspective, which will be used to estimate the lifetime incremental costs and QALY gains associated with smoking cessation, as applied in previous economic evaluations of smoking cessation interventions.

### Ethical considerations

There are several ethical considerations associated with this study. To promote an active control group in which the participants receive a usual standard of care, we have elected to expose all participants to the Royal Australian College of General Practitioners Ask, Advise, Help model. Furthermore, both control and SRG group participants will be offered free access to the mindfulness smartphone application after completing the study, should it prove to be of benefit. We also acknowledge that we are studying a vulnerable group. During the ongoing process evaluation, we will “check in” with participants who have dropped out of the interventions to explore how our procedures might be adapted to address any problems they encountered that led to their dropping out and facilitate positive changes in psychological wellbeing. Acknowledging the economic vulnerability of the participant group, we offer intervention group participants who are required to engage with the study via Zoom will be compensated for their data usage with $50 gift cards upon completion of the baseline survey and attendance at their first small group session. For participants who complete the 18-month study, a lottery will be drawn to randomly select winners of supermarket vouchers to the value of $300, $200 and $100. In addition, all control group participants who complete the study will be entered in a lottery to win 1 of 3 x $100 supermarket vouchers to reduce the risk of differential drop-out between study groups. Furthermore, we offer a small reimbursement of $20 to participants who engage with the process evaluation of phase 2 (peer-led blogs).

Study data will be stored on an encrypted drive to maintain confidentiality. The final trial dataset will be accessible by the investigation team. The Project Reference Group members who are external to the research team will function as the Data Monitoring Committee (DMC). The group is comprised on representatives from stakeholder organisations working in tobacco control in addition experts in mindfulness and goal setting interventions. The primary funder will nominate a representative for an observer-only role. The group will provide advice on the project’s feasibility and utility for stakeholder groups considering policy issues, translation of findings, and overall impact on low SES smokers. A formal DMC will not be established due to the minimal risk-levels of the interventions.

### Dissemination

We intend to disseminate the results in peer-reviewed journal articles, press releases, and meetings with stakeholders. Any future amendments this protocol will be found in the relevant trial registry.

### Registration

This study has been registered with the Australian New Zealand Clinical Trials Registry (Trial ID: ACTRN12621000445875). The Universal Trial Number is U1111-1261–8951.

## Discussion

To our knowledge, this study will be the first to compare the efficacy of smoking cessation interventions that are designed to address resilience for low SES smokers, which have been identified by them as acceptable. It will use a randomised controlled trial method in an online delivery format and include peer mentors from the same SES group. The inclusion of psychological and other measures will facilitate exploration of the mechanisms of impact, with a particular focus on the importance of resilience. We expect that the comprehensive picture describing change over time and in response to different interventions, in tandem with the process evaluation, will allow us to determine both efficacy and barriers to translation. If efficacy is established, knowledge of barriers will enable us to further tailor the content and administration of the interventions. By intervening within the framework of the Psychosocial Model of Resilience, we are applying a promising new paradigm to a prominent and inequitable public health problem.

We anticipate several difficulties. Most notably, the interventions will be administered online rather than face-to-face due to social restrictions imposed by the COVID-19 pandemic. This constraint raises questions over the generalisability for face-to-face setting and accessibility to those without ready access to the internet. Nonetheless, testing the efficacy of the interventions in an online setting is important because it reflects real world changes in the way services are provided and supports the inclusion of geographically remote participants. There is evidence that online interventions are effective for addiction treatment (including smoking [70]), and furthermore, there is growing evidence that internet-based CBT can be equivalent to face-to-face CBT in treating a range of psychological problems. [71] Other potential problems raised by the online delivery are lower adherence with intervention protocols and higher drop-out rates. [72] We will try to improve adherence with text message reminders of session times and in-session reminders to complete homework. For the two mindfulness-based interventions, the addition of a recently developed smartphone application provides a simple and user-friendly access route that encourages the completion of homework. We will address the possible attrition bias by using a modified intention-to-treat analysis protocol, whereby participants who drop out of the study will continue to be followed for data collection purposes. We will only request data from participants who have completed the baseline survey.

To summarise, this study aims to test the efficacy of mindfulness and goal-setting interventions with low SES smokers. We will examine the practical application of the interventions to low SES smokers by performing a process evaluation and assessing cost-effectiveness and cost-utility. We expect that our assets-based approach to smoking cessation can guide future public health programs to reduce the prevalence of smoking-related health problems and ameliorate the socioeconomic inequities which continue to be associated with smoking.

## Data Availability

Deidentified data will be available from though the ANZCTR.

## Abbreviations

DMC: Data monitoring committee
CBT: Cognitive behavioural therapy
MiCBT: Mindfulness-integrated cognitive behavioural therapy
MT: Mindfulness training
QALY: Quality adjusted life year
SACHREC: Southern Adelaide Clinical Human Research Ethics Committee
SES: Socioeconomic status
SMART: Specific, measurable, attainable, realistic, time-bound
SRG: Setting realistic goal
